## Abstract

**Introduction:**

Consolidation of motor skill learning, a key component of rehabilitation post-stroke, is known to be sleep dependent. However, disrupted sleep is highly prevalent after stroke and is often associated with poor motor recovery and quality of life. Previous research has shown that digital cognitive behavioural therapy (dCBT) for insomnia can be effective at improving sleep quality after stroke. Therefore, the aim of this trial is to evaluate the potential for sleep improvement using a dCBT programme, to improve rehabilitation outcomes after stroke.

**Methods and analysis:**

We will conduct a parallel-arm randomised controlled trial of dCBT (Sleepio) versus treatment as usual among individuals following stroke affecting the upper limb. Up to 100 participants will be randomly allocated (2:1) into either the intervention (6–8 week dCBT) or control (continued treatment as usual) group. The primary outcome of the study will be change in insomnia symptoms pre to post intervention compared with treatment as usual. Secondary outcomes include improvement in overnight motor memory consolidation and sleep measures between intervention groups, correlations between changes in sleep behaviour and overnight motor memory consolidation in the dCBT group and changes in symptoms of depression and fatigue between the dCBT and control groups. Analysis of covariance models and correlations will be used to analyse data from the primary and secondary outcomes.

**Ethics and dissemination:**

The study has received approval from the National Research Ethics Service (22/EM/0080), Health Research Authority (HRA) and Health and Care Research Wales (HCRW), IRAS ID: 306 291. The results of this trial will be disseminated via presentations at scientific conferences, peer-reviewed publication, public engagement events, stakeholder organisations and other forms of media where appropriate.

**Trial registration number:**

NCT05511285.

Strengths and limitations of this studyUse of an evidence-based therapy to improve sleep symptoms.Home-based intervention, which reduces burden on participants.Unable to blind participants to the treatment group.Motor training component of the trial is optional and, therefore, will likely have a reduced sample size.

## Introduction

Stroke is one of the leading causes of long-term disability worldwide, often resulting in prolonged cognitive, motor and emotional problems.^1^ Many stroke survivors also experience long-term sleep disruption,^2–4^ with the prevalence of post-stroke insomnia, a sleep disorder characterised by difficulties initiating and maintaining sleep, estimated to be as high as 60%.^5–7^ Poor sleep after stroke is frequently associated with motor/cognitive impairments, mood disorders such as anxiety and depression and a reduced quality of life.^8–10^ There is also appreciable evidence to suggest that those who have poorer sleep show worse rehabilitation outcomes,^8 11^ which we hypothesise may be, at least in part, due to the importance of sleep for learning and memory processes.

Motor learning—the process of learning new, or relearning old, motor skills—is an integral part of post-stroke rehabilitation.^12^ Improvements in motor performance not only occur during practise itself but also during periods of rest, including sleep.^13^ In recent years, a large body of evidence has emerged, indicating these latter improvements in performance, better known as consolidation, are sleep-dependent.^14–21^ Mechanistically, the consolidation of motor learning during sleep is thought to occur via ‘reactivations’ of neural activity elicited during initial learning, with stronger reactivation correlating to a greater degree of memory consolidation.^20 22^ Therefore, it stands to reason that consolidation of motor memories after or between therapy sessions may be impaired post-stroke, via direct disruption of these biological processes that occur during sleep, thus hindering recovery. Indeed, recent results from our lab have demonstrated that sleep disturbances during rehabilitation after acquired brain injury are associated with poorer motor recovery outcomes.^8^ Together these findings suggest that improving sleep quality post-stroke could potentially also help to enhance rehabilitation outcomes. However, research and interventions focused on improving symptoms of post-stroke insomnia are lacking.

Cognitive behavioural therapy (CBT) is a National Institute for Health and Care Excellence (NICE) recommended, first-line treatment for those with insomnia disorder^23–25^ and is supported by a wealth of evidence for improving symptoms in otherwise healthy individuals.^26 27^ Considering that few patients receive access to therapist-delivered CBT due to systemic barriers,^28 29^ fully-automated digital CBT (dCBT) has the potential to provide access to evidence-based treatment at scale. We, and others, have shown that the delivery of dCBT can improve insomnia symptoms,^30 31^ psychological well-being,^32 33^ cognitive function^34^ and is also feasible to use after stroke.^35^ Furthermore, preliminary data suggest that dCBT is also efficacious at improving self-reported measures of sleep and mood in adult, community dwelling, stroke survivors when compared with provision of sleep hygiene information.^36^

### Study objectives

Given the possible benefit of improved sleep on recovery of motoric function after stroke, the overall aim of the present study is to explore the potential for sleep improvement, via dCBT, to impact on rehabilitation outcomes post-stroke. Termed INSPIRES-2 (improving sleep and learning in rehabilitation after stroke, part 2), we will more specifically aim to:

Test whether symptoms of insomnia are improved in stroke survivors following dCBT in comparison to treatment as usual.Assess whether overnight consolidation of motor learning is improved after the delivery of dCBT in comparison to treatment as usual.Determine whether actigraphy-derived sleep measures are improved after the delivery of dCBT in comparison to treatment as usual.Identify whether changes in sleep following dCBT correlate with changes in overnight consolidation of motor learning.Test for changes in symptoms of depression and fatigue after dCBT in comparison with treatment as usual.Explore the feasibility and potential effect size estimates of at-home motor training following dCBT or usual care.

## Methods and analysis

### Participant recruitment

Up to 100 participants with stroke affecting the upper limb will be recruited. Participants will be identified via: National Health Service (NHS) patient identification centres, from prior study involvement at the Wellcome Centre for Integrative Neuroimaging (WIN) or Cognitive Neuropsychology Centre (University of Oxford), social media, stroke support groups and word of mouth. Participants may be identified at any time following their stroke but will not be enrolled in the study until they have been discharged from inpatient care. There is no specific post-stroke period restriction for recruitment to this trial.

The trial opened to recruitment in September 2022, with a planned trial end date of December 2024. The study was registered on 22 August 2022 (prior to recruitment of the first participant).

#### Inclusion/exclusion criteria

Participants must be 18 years of age or above, discharged from inpatient care and have a clinical diagnosis of stroke affecting the upper limb. Participants should, however, have sufficient movement to be able to perform the prescribed motor learning task. Individuals must be willing and able to give informed consent for participation in the study. Participants should also be interested in accessing a programme intentionally aimed at improving sleep quality and given the nature of the study, have reliable access to the internet. Individuals may not enter the study if any of the following apply: diagnosis of other neurological condition/s affecting movement (eg, Parkinson’s disease) or untreated diagnosed sleep disorder/s (eg, sleep apnoea); experience uncontrolled seizures; have engaged in psychological therapy for insomnia in the past 12 months; are pregnant or have planned inpatient admission (eg, for rehabilitation) in the next 4 months that would impact on the ability to engage with the dCBT programme.

#### Sample size distribution

Based on prior work in our lab comparing dCBT with sleep hygiene information in stroke survivors^36^ and other studies involving dCBT in people who suffer from insomnia, we estimate a medium between group effect size of d=0.7. In order to achieve this, a sample size of n=76 will be required (α=0.05, power=80%, 2:1 random allocation ratio dCBT:control, two-tailed independent samples t-test). A sample size of n=100 was selected to accommodate an approximate 25% dropout rate (determined from previous research experience). As the at-home motor training component of the trial is optional, we expect the resultant sample size to be reduced.

### Trial design

This study will be conducted as a randomised controlled trial with two parallel study arms: (1) digital cognitive behavioural therapy for insomnia (dCBT; experimental condition) and (2) treatment as usual (treatment as usual; control condition), see figure 1. The trial will, therefore, be dCBT+treatment as usual versus treatment as usual only and is reported in accordance with the Standard Protocol Items: Recommendations for Interventional Trials checklist^37^ (see online supplemental file 1). Participants will receive a version of the participant information sheet and can ask the researchers any questions they may have. Electronic informed consent is obtained from the participant (using Jisc) before any study-specific procedures are performed (online supplemental file 2).

10.1136/bmjopen-2023-071764.supp1Supplementary data

10.1136/bmjopen-2023-071764.supp2Supplementary data

**Figure 1 F1:**
[figure not shown]
Flowchart of the trial, depicting patient recruitment, screening, intervention, assessments and optional motor training. ARAT, Action Research Arm Test; BBT, Box and Blocks Test; dCBT, Digital Cognitive behavioural Therapy; FSS, Fatigue Severity Scale; 9HPT, Nine-Hole Peg Test; mRS, Modified Rankin Scale; PHQ-9, Patient Health Questionnaire; SCI, Sleep Condition Indicator; STOP-Bang, Obstructive Sleep Apnoea Questionnaire.

Baseline measures of sleep will be obtained via completion of the Sleep Condition Indicator (SCI^38^) and 7-night actigraphy recordings (measuring estimated total sleep time, wakefulness after sleep onset (WASO) and sleep fragmentation index). For the actigraphy, a waterproof monitor (MotionWatch V.8, CamNTech) will be delivered to participants to be worn on their least affected wrist. Participants will also complete a sleep diary (paper or digital), detailing approximately what time they attempted sleep and woke up for each of the seven nights. Mood and fatigue will be assessed using the Patient Health Questionnaire (PHQ-9^39^) and the Fatigue Severity Scale (FSS^40 41^), respectively.

We will assess consolidation of motor learning using the commercial rehabilitation device; GripAble (GripAble Ltd). At home, participants will complete a learning task called Balloon Buddies^42^ at specific times of day. The task will require participants to squeeze and release the GripAble device (a hand grip dynamometer) with their affected hand in order to direct an avatar, which appears on an associated tablet, towards targets set along a predetermined path. In each attempt of the task, participants can score up to 50 points. The score participants achieve will be displayed on the screen at the end of each task attempt. We will randomly assign participants to complete one of three different ‘levels’ of the task, which only differ in regards to the target path but not in difficulty. Before starting the task, the GripAble will be calibrated to each participants’ individual grip and release strength/ability. Participants will be instructed to first complete the task in the evening (between 20:00 and 22:00 or at least 30 min prior to sleep). They will complete the task 10 times (recording how many targets they hit each time), lasting no longer than 30 min. Pilot data in a previous sample of stroke survivors with upper limb impairment indicate significant improvements in accuracy over 10 repetitions (figure 2). They will then be asked to perform a retest the next morning (between 8:00 and 10:00 or at least 30 min after wake), completing the same task a further five times. Again, we will ask participants to record their scores and the retest should take less than 15 min.

**Figure 2 F2:**
[figure not shown]
Number of targets hit (maximum 50) per repetition of the GripAble motor learning task in a sample of stroke survivors with upper limb impairment. Mean scores indicated by filled circles±standard error (sample size: n=25).

Age, sex, ethnicity, date of stroke/s, stroke symptom laterality, modified Rankin Scale(mRS) and current medications will also be collected. Additionally, we will use the STOP-Bang questionnaire^43^ to assess the potential risk of obstructive sleep apnoea and a further sleep disorder questionnaire^44^ to screen for sleep conditions other than insomnia. All demographic information will be collected and stored using online questionnaires (Jisc) or over the phone depending on the participants’ preference. Additionally, all equipment will either be sent to the participants’ homes or delivered by a researcher (depending on location and preference) and will be collected in person on completion or return postage will be organised.

#### Randomisation and blinding

Following baseline assessments, participants will be randomised at a 2:1 ratio (experimental:control) using an online randomisation software (rando.la), with minimisation of between group differences in age, sex, baseline SCI score and time since stroke (months). Once randomised, each participant will be assigned a sequentially numbered study ID. It is not possible to blind the researchers involved in the day-to-day running of the study or the participants to their intervention group. Analysis will be carried out by an individual not involved in day-to-day research activity and not explicitly informed of the experimental condition.

### Intervention

For the intervention group, participants will be asked to continue any of their usual treatments. In addition to this, they will be provided with access to the commercially available dCBT programme, Sleepio (Big Health Ltd). The programme involves six sessions of automated dCBT, with a virtual professor, and access to a daily online sleep diary. dCBT sessions become available 7 days following completion of the previous session. Participants may also interact with an online community and library of resources. Participants will be provided with a web link to the programme and will need to sign up by entering their name, email address and a predetermined participant ID. As part of the dCBT programme, participants will be required to complete a daily online sleep diary for the duration of the programme and watch weekly videos pertaining to dCBT. Based on feedback from previous studies, they will also receive a booklet with additional details that may be useful for accessing the programme.

The control group will be asked to continue to adhere to their treatment as usual, with no further intervention measures specific to the research. The exact nature of this treatment will vary across participants. At post-intervention, we will ask whether participants in the control group received any treatment for their sleep. Participants in the control group will be provided the opportunity to access the dCBT programme after completing the study; however, no data will be recorded from this.

### Post-intervention

Approximately 10 weeks following randomisation, assessments of sleep (SCI, 7-night actigraphy, sleep diary), mood (PHQ-9), fatigue (FSS) and motor consolidation (GripAble task) will be repeated. Participants will be randomly assigned a different level of motor learning task, so that the movement pattern is different to that which they learnt at baseline. Any participants who have not completed the dCBT programme by 10 weeks (or do not wish to complete it) will still be given the opportunity to complete the post-intervention assessments. Once completed, any equipment will be picked up by a researcher or return postage organised (dependent on participant preference, location and desire to complete voluntary training, see next section).

### Optional motor training

Before completion of the post-intervention assessments, all participants—regardless of group allocation—will be offered 4 weeks of home-based upper limb training. This training will involve daily use of the GripAble rehabilitation device and target a wide range of hand and arm movements. Participants will be asked to attempt to perform 1 hour of training per day, either in one session or broken up into shorter sessions throughout the day. Depending on their level of impairment, participants will be instructed by a researcher, which games on the device will be most suitable and how to access them, but participants are free to explore the device as they wish. We will also ask participants to complete a training diary to record how many times they use the device each day and to estimate how long they spent practising each day in total. Participants access the device through a research account, which allows the research team access to a dashboard of data. We will use the dashboard information to record the amount of time spent on each task and the number of movement repetitions performed each day. If participants decide to engage in this training, assessments of upper limb function will be conducted using the Action Research Arm Test (ARAT^45^), Box and Blocks Test (BBT^46^), The Nine-Hole Peg Test (9HPT^47^) and range of movement using the GripAble device (pronation/supination, wrist flexion/extension, radial/ulnar deviation and grip squeeze (strength) and release (%)). These assessments will be collected in-person, during the post-intervention visit when actigraphy and GripAble devices are delivered and repeated approximately 4 weeks later after completion of the training programme. Data from the optional training intervention will help to inform protocols and effect size estimates of future studies combining sleep improvement and at-home rehabilitation programmes.

### Outcome measures

The primary outcome of this study will be self-reported insomnia symptoms pre to post intervention compared with treatment as usual, measured via SCI scores.^38^ SCI data will be collected during baseline assessments and approximately 10 weeks after randomisation, following either the dCBT intervention or treatment as usual. SCI has been shown to be a robust screening tool for the clinical evaluation of insomnia, with an estimated magnitude change of 7 scale points representing a meaningful improvement in insomnia symptoms.^48^ Higher values on the SCI indicate fewer symptoms of insomnia and a score of 16 or below suggests probable insomnia.^38^

Secondary outcome measures include: change in overnight motor memory consolidation between groups; changes in actigraphy-derived sleep measures (estimated total sleep time, WASO and sleep fragmentation index) between groups; correlations between changes in SCI and actigraphy-derived sleep measures and overnight motor memory consolidation in the dCBT group and changes in symptoms of depression and fatigue between the dCBT and control groups. Overnight motor consolidation will be determined by changes in performance on the GripAble motor learning task from evening training to morning retest,^49^ measured at baseline and approximately 10 weeks following randomisation. Actigraphy-based sleep measures at baseline and approximately 10 weeks following randomisation will be extracted and analysed using custom software, MotionWare (CamNTech Ltd) and corroborated with sleep diary entries. The PHQ-9 and FSS, measured at baseline and approximately 10 weeks following randomisation, will be used to measure changes in depression and fatigue between the dCBT and control groups. In addition to these secondary outcomes, we intend to measure the adherence and efficacy of at-home motor training during the optional intervention as an exploratory outcome. Training diaries and changes in upper limb function (ARAT, BBT and 9HPT scores) will help to determine feasibility and potential effect size estimates.

### Data analysis

#### Primary outcome

The primary outcome, SCI score at post-intervention, will be analysed using intention-to-treat (ITT). An analysis of covariance (ANCOVA) will be used to test whether self-reported symptoms of insomnia are improved for the dCBT group in comparison to the control group. The model will test for differences in SCI scores between groups at the post-intervention time point (~10 weeks following randomisation), with baseline score, sex and time since stroke added as covariates. All ANCOVAs will be run in general linear model format.

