#### Secondary/exploratory outcomes

Secondary outcomes will be tested using a complete-case ITT population, including all participants for whom data are available at the post-intervention timepoint (irrespective of whether they completed the intervention or not). To test for changes in motor consolidation, we will determine the difference in performance from the end of evening training relative to the morning retest on the GripAble motor learning task at each time point. To determine whether motor consolidation improves for the dCBT group compared with control, we will use an ANCOVA. The model will test for between-group differences at post-intervention (~10 weeks following randomisation), with baseline consolidation score as a covariate. Changes in actigraphy-derived sleep measures will also be analysed using an ANCOVA, testing for differences between groups at 10 weeks following randomisation with baseline scores added as covariates. To explore whether the magnitude of changes in sleep measures relate to changes in motor consolidation, we will use correlational analysis (either Spearman’s or Pearson’s correlations as appropriate), testing for associations between changes in SCI and actigraphy-derived sleep measures (estimated total sleep time, WASO and sleep fragmentation index) with changes in motor consolidation. Changes in symptoms of depression and fatigue in the dCBT group compared with the control group will also be analysed using an ANCOVA to examine differences between groups on the PHQ-9 and FSS at follow-up, with baseline score added as a covariate. For all analyses, we will include covariates such as age, sex, time since stroke, etc as required.

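### The primary ANCOVA leaves out age, a minimisation factor, and the secondary ANCOVAs have no closed covariate list; the cost is small and conservative, and the repair is nearly free

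*Protocol article*

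**What the plan says.** Under Randomisation and blinding, participants are allocated 2:1 "with minimisation of between group differences in age, sex, baseline SCI score and time since stroke (months"). That makes four balancing factors.

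Under Data analysis, Primary outcome, post-intervention SCI is compared between groups by ANCOVA "with baseline score, sex and time since stroke added as covariates". Three of the four factors are there; age is not, and its absence is not explained.

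Under Secondary/exploratory outcomes, each ANCOVA is tied to its own baseline only: motor consolidation "with baseline consolidation score as a covariate", the actigraphy measures "with baseline scores added as covariates", and PHQ-9 and FSS "with baseline score added as a covariate". The section then closes with: "For all analyses, we will include covariates such as age, sex, time since stroke, etc as required". It gives no rule for when a covariate is required and does not close the list. Baseline SCI, itself a minimisation factor, is not named for any secondary ANCOVA, even in this clause.

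**The concern.** Minimisation makes the arms more alike on the chosen factors than simple randomisation would. If such a factor predicts the outcome, its contribution is largely removed from the treatment contrast. If it is then left out of the model, its variation stays in the residual variance. The reported standard error is larger than the estimator's true variability, the interval is too wide and the test rejects too seldom. The usual remedy is to adjust for every factor used in allocation. Here the analysis and the allocation scheme differ by one factor in the primary model and by up to four in the secondary models.

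The second issue is openness. A list ending in an unspecified remainder, with no rule for inclusion, allows the secondary models to be settled after the data are seen. Because the clause speaks of all analyses and names age first, a reader may also be unsure whether age can enter the primary model.

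**Working it through.** **Inputs from the protocol article (Sample size distribution).** The article says "we estimate a medium between group effect size of d=0.7" and gives "α=0.05, power=80%, 2:1 random allocation ratio dCBT:control, two-tailed independent samples t-test", with 76 evaluable out of 100 recruited. **Assumed, because the article does not give it:** r, the partial correlation of age with post-intervention SCI given the other covariates, taken from 0 to 0.5.

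**Step 1: reproduce the stated sample size.** Normal approximation: n(control) = (1 + 1/2)(1.960 + 0.842)² / 0.7² = 24.03, rounded up to 25, total 75. The noncentral t calculation gives 24.7 controls, total 74.1. With 25 and 51 per arm (76), power is 80.8%. The stated 76 reproduces.

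**Step 2: analytic effect of adding age.** The standard error is multiplied by √(1 − r²), so the effective d is 0.7/√(1 − r²). If age were perfectly balanced and then omitted, the true test size would be 2[1 − Φ(1.96/√(1 − r²))], which is the worst case.

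| r | SE narrows by | Power at 76 with age | Worst-case test size, age omitted |
|---|---|---|---|
| 0 | 0% | 80.8% | 5.0% |
| 0.1 | 0.5% | 81.2% | 4.9% |
| 0.2 | 2.0% | 82.3% | 4.6% |
| 0.3 | 4.6% | 84.3% | 4.0% |
| 0.4 | 8.3% | 87.0% | 3.3% |
| 0.5 | 13.4% | 90.5% | 2.4% |

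**Step 3: simulation with imperfect balance and dropout.** 3000 trials of 100 participants, 2:1 biased-coin minimisation on the four factors (continuous ones in three categories), 76% retained at random, ANCOVA with and without age. The SD given the primary model's three covariates is set to 1, so d = 0.7 is in those units.

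| r | Model SE / empirical SE, age omitted | Test size, omitted v included | Power, omitted v included |
|---|---|---|---|
| 0.1 | 0.2456/0.2456 = 1.00 | 5.5% v 5.5% | 79.3% v 79.6% |
| 0.2 | 0.2456/0.2436 = 1.01 | 5.6% v 5.5% | 79.4% v 80.8% |
| 0.3 | 0.2456/0.2403 = 1.02 | 5.4% v 5.5% | 80.0% v 82.7% |
| 0.4 | 0.2457/0.2354 = 1.04 | 4.5% v 5.5% | 80.7% v 85.2% |
| 0.5 | 0.2457/0.2290 = 1.07 | 3.7% v 5.5% | 81.4% v 89.0% |

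Monte Carlo error on test size is about 0.4 points. The same simulated allocations and errors serve every row, so the 5.5% in the models with age is a shared chance offset. With realistic balance and dropout, conservatism becomes visible only from about r = 0.4.

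Part of the narrowing in Step 2 corrects an overstated standard error and part is a real gain in precision. At r = 0.4 the model SE falls from 0.2457 to 0.2257 (8.1%), while the empirical SE falls from 0.2354 to 0.2265 (3.8%).

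**Step 4: is the planned power at risk?** The 76 comes from an unadjusted t-test, whereas the primary model already adjusts for baseline SCI. In a separate simulation (4000 trials, 76 minimised, no dropout, baseline SCI assumed to explain 30% of variance and age 10%), the SE is 0.2045 without age and 0.1899 with it. With a t critical value of about 1.99:

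- without age: 0.7/0.2045 = 3.42, and Φ(3.42 − 1.99) ≈ 92%
- with age: 0.7/0.1899 = 3.69, and Φ(3.69 − 1.99) ≈ 95%

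That assumption about age is strong: its partial r is √(0.10/0.70) = 0.38. Even so, the planned model is above 80%.

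**The case against.** The strongest reply is that little follows from the mismatch. The article gives no evidence that age predicts SCI change, the effect is negligible at r up to about 0.2, and any departure from 5% is on the safe side. All of that stands.

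Four stronger readings are tempting, and the document does not support them.

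- **That the omission wastes power in a trial with none to spare.** Step 4 shows otherwise: baseline adjustment is not credited in the sample size, and if it explains 30% of variance the planned model has about 92% power without age.
- **That the open clause contradicts the primary covariate list.** The clause closes the section on secondary and exploratory outcomes, and the primary model has its own heading and a closed list. The natural reading is all analyses in that section. The wording is loose enough to need a clarifying sentence, but a contradiction is only one reading.
- **That results will drive covariate choice in every analysis.** The clause permits late choice in the secondary models; it does not show that this will happen. The analyst is meant to stand apart from daily study activity and is not explicitly told the condition, which lowers the risk without removing it.
- **That time since stroke must be log-transformed.** Recruitment has no time limit after stroke, but no distribution is given. This is optional and not part of the correction.

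It may also be said that secondary covariates belong in a statistical analysis plan that is not shown. A full list could indeed be left to it. But the article states covariate sets of its own, and these do not match its own allocation scheme. Putting baseline SCI into every secondary model is a defensible convention that follows from the allocation scheme, not the only acceptable choice.

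**Conclusion.** The point holds as a low-cost improvement. Age is a minimisation factor left out of the primary ANCOVA without explanation, and the secondary ANCOVAs lack a closed covariate set. For the primary outcome the consequence is a standard error that is somewhat too wide and a slightly conservative test, with no bias and no excess of false positives. Adding age would narrow the standard error by about 0.5% to 8% for an assumed r of 0.1 to 0.4. These sizes rest entirely on the assumed r and on age acting linearly. No size was computed for the secondary outcomes; up to four balancing factors are missing there, so the effect could add up, but by how much is unknown.

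**What to change.** - **Primary outcome:** add age, so that the ANCOVA contains all four minimisation factors. If age was left out on purpose, give the reason.
- **Secondary outcomes:** in each ANCOVA fix the outcome's own baseline plus age, sex, baseline SCI and time since stroke.
- **Open clause:** replace it with that list, state that it does not alter the primary model, and label any other adjustment as a sensitivity analysis.

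The cost is about one sentence in each of the two analysis sections. All the variables are collected at baseline, before randomisation. The primary model loses one degree of freedom (71 to 70 residual at 76 participants); if age is unrelated to the outcome, the simulated SE rises only from 0.2456 to 0.2463. Each secondary model spends four more degrees of freedom. The sample size does not change.
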